4. The Physical Health and Mental Health Scores are then calculated by multiplying the respective Physical Health and Mental Health Sum by 10 and adding 50 to the product. A patient with responses typical of a general population will have a score of 50 and perfect health would correspond to Physical Health and Mental Health Scores of 57.87 and 62.14 respectively.

Whilst reference means for a US population are to be applied it has been shown that their application to a UK population gives nearly identical results for the Physical Health and Mental Health Score compared to the use of UK specific reference means.

Any patient who has died before the respective timepoint will be assigned a 0 recoded score for each item of the SF-36 prior to deriving the Physical Health and Mental Health Scores.

If less than 50% of the SF-36 questions are completed at a given timepoint or no responses are completed for an individual subscale, the SF-36 data will not be included in the analysis for that patient at that timepoint. If  $\geq 50\%$  of the SF-36 questions are completed, the mean of the observed individual item recorded scores within the respective subscales will be applied to the algorithm.

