## EVG001SAH Statistical Analysis Plan

other specified problems; these will not be used in the analysis. Data will be analysed separately for emotional and cognitive problems. The number of questions, within each subscale, that has a response of either ‘Yes, severely hindering daily life’ or ‘Yes, but not severe’ will be calculated and this number will be recoded to a CLCE score as described in Table 7. The CLCE-24 score will be subject to statistical analysis.

If a patient dies before a given timepoint they will be assigned a score of 3. If less than 50% of the CLCE-24 questions are completed at a given timepoint the data will not be included in the analysis for that patient at that timepoint. Otherwise, the percentage of responses will be calculated using 24 as the denominator. In determining evaluability, a response of ‘I am not sure’ will be considered a completed response.

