## 5.9 BICRO-39

The Brain Injury Community Rehabilitation Outcomes Scale (BICRO-39) is recorded at 90 and 180 days and consists of 39 questions scored from 0= the most favourable response (no help or prompts, once a week or more, most or all days, several hours a day, more than 20 hours a week, never - as appropriate) to 5=the least favourable response (don’t do at all, not applicable or never, almost always – as appropriate). The BICRO-39 is divided into 8 subscales as presented in Table 8. The subscale score is calculated as the mean of the individual scores within that subscale.

An overall score will also be calculated as the mean score across the 34 individual scores that are not included in the contact with partner/children and contact with parents/siblings subscales. These scales are excluded as the desirable direction may vary between patients; some patients may wish to be less reliant on carers if they are relatives and in others alienation from family member maybe a problem^6.

Any patient who has died before the respective timepoint will be assigned a subscale and an overall score of 5 corresponding to the worst outcome. If less than 50% of the 39 questions are completed at a given timepoint, or no questions have been answered in one of the 6 subscales contributing to the overall score, none of the BICRO-39 data will be included in the analysis at that timepoint. Otherwise, if ≥50% but less than 100% of the BICRO-39 questions are completed, the mean of the recorded scores within the respective subscales will be used in the analysis of subscales. However in this case, the overall score will be calculated as a weighted average of the individual subscale scores with weights of 6/34 for all subscales included apart from productive employment which receives a weight of 4/34. This approach ensures that if missing data predominates in one subscale its contribution is not down-weighted in the overall score.

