### **5.10 Subarachnoid Haemorrhage Outcomes Tool**

The Subarachnoid Haemorrhage Outcomes Tool (SAHOT) is recorded at Day 28, 90 and 180. days and consists of 56 questions scored 0 for ‘No change’, 1 for ‘Some change’ and 2 for ‘Large or severe change’. The only possible exception is the ‘Quality of relationship with those closest’ question, which, if the subsequent question indicates the relationship is better, will be scored as 0 regardless of the response.

The sum of the scores across all 56 questions is calculated to give a raw total score and depending on the outcome corresponds to a SAHOT category (Table 9), which be analysed statistically. If the patient has died prior to the timepoint they are assigned to the worst category of 9.

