## **6.7 Missing Data Diagnostics**

For the mRS, GOSE, SAHOT, CLCE, BICRO and SF-36 endpoints, if more than 15% of patients have missing data for the respective endpoint in either treatment arm at Day 180, the possible impact of these data on the primary analyses will be explored as follows:

- For all endpoints the number of patients with missing data will be summarised. In addition, baseline WFNS score (1-3 v 4-5) will be summarized by treatment arm for each endpoint at each timepoint according to whether data were missing at that timepoint.
- For mRS and GOSE only the analysis at each timepoint will be repeated by carrying forward the outcome from the most recent timepoint with recorded data.

The purpose of these analyses is to assess whether the amount of missing data differs by treatment arm and whether patients with missing data initially had a worse prognosis or were performing worse on other measures recorded at the same timepoint. For example, if there

are more patients in the placebo arm with missing data and those that have missing data were tending to respond less well, this would suggest the treatment effect may have been underestimated.

If the results are marginal for a particular endpoint these investigations may be performed despite neither arm having 15% of patients with missing data. Dependent on results further analyses may be performed to assess the possible impact of missing data.

For TCD endpoints it is not anticipated that missing data could have a bearing on the outcome of the results given the proximity of the measurements to dosing.

Only the year of birth has been recorded. When calculating age, a date of birth of 1st July will be assumed.

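### Four questionnaire endpoints score deaths but drop living patients with too few answers, and no fixed re-analysis covers the case where severe disability is the reason

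*SAP*

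**What the plan says.** **Deaths are kept.** On the SF-36 (section 5.7) a patient who has died "will be assigned a 0 recoded score for each item of the SF-36", and these zeros then go through the weighted algorithm. On the CLCE-24 (5.8) death scores 3, and on the BICRO-39 (5.9) it scores 5. On the SAHOT (5.10), "If the patient has died prior to the timepoint they are assigned to the worst category of 9".

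**Living patients with too few answers are removed.**
- SF-36: with under half the items answered, or any subscale left empty, "the SF-36 data will not be included in the analysis for that patient at that timepoint".
- CLCE-24: "If less than 50% of the CLCE-24 questions are completed at a given timepoint the data will not be included in the analysis".
- BICRO-39: with under half the items answered, or one of the six contributing subscales empty, "none of the BICRO-39 data will be included in the analysis at that timepoint".
- SAHOT: the rule under Table 9, read literally, removes a form when fewer than half of its items are missing. The intent is evidently the reverse. An empty subscale also removes the form.

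None of these rules asks why the form is incomplete.

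**Missing-data plan (section 6.7 and Table 11).** Above 15% missing at Day 180 in either arm, missing patients are counted and baseline WFNS is summarised by missingness. If results are marginal, the same work may be done below 15%, and further unspecified analyses may follow. A re-analysis is fixed for two other endpoints only: "For mRS and GOSE only the analysis at each timepoint will be repeated by carrying forward the outcome from the most recent timepoint".

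**The concern.** The trial includes WFNS 4-5 patients, and its own scales have living grades for very severe disability (mRS 5, GOSE 2 and 3). If such patients tend not to return a usable form, the group between poor completers and the dead leaves the analysis while the dead stay in. Whether a patient is analysed then depends on a post-randomisation outcome that treatment may change.

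The distortion can run either way. A treatment that lifts patients from unable to respond to just able to respond adds poor scores to its own arm. A treatment that turns deaths into severe survival removes bad scores and puts nothing in their place.

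Section 6.7 sees the risk. Its stated purpose includes learning whether patients with missing data were doing worse on other measures at the same timepoint. Yet the diagnostics it lists for these four endpoints use only counts and baseline WFNS, neither of which answers that question.

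**Working it through.** **1. Reproduce the plan's own SF-36 figure.** Inputs are the means, SDs and coefficients in Table 6. Score = 50 + 10 × Σ coefficient × (X - mean)/SD. With every subscale at 100 this gives 57.87 and 62.14, matching the SAP's statement that "perfect health would correspond to Physical Health and Mental Health Scores of 57.87 and 62.14 respectively".

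**2. SF-36 score given to a death.** Set every X to 0. For Physical Health (PH) the terms coefficient × mean/SD are PF 1.566, RP 0.844, RE -0.473, VT 0.084, EW -0.917, SF -0.028, BP 1.017 and GH 0.893. They sum to 2.986, so PH = 50 - 29.86 = 20.14. The same steps give Mental Health (MH) = 17.34.

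These are not the lowest possible scores, because some weights are negative:
- Formula minima (positively weighted subscales at 0, negatively weighted at 100): PH 1.73, MH -1.26.
- Living patient with PF, RP, BP, GH and VT at 0 and RE, EW and SF at the reference means: PH = 50 - 10 × (1.566 + 0.844 + 0.084 + 1.017 + 0.893) = 5.96, below a dead patient.
- Living patient with RE, EW, SF and VT at 0 and the physical subscales at the reference means: MH 2.21, also below a dead patient.

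**3. CLCE-24 ceiling.** Section 5.8 uses 24 as denominator. The emotional part has 9 items, so a living patient reaches at most 9/24 = 37.5%, which is score 2 in Table 7. Score 3 on that part is reachable only by death. On the cognitive part 13/24 = 54.2%, so a living patient can tie with death at 3.

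**4. Effect of dropping living non-completers.** The SAP gives no outcome or completion rates, so the counts are assumed. There are 45 per arm (90 evaluable patients, equal allocation assumed). Ordered groups are good / moderate / poor but completed / living non-completer / dead, and the control arm is 19 / 10 / 6 / 6 / 4. Net win probability = (pairs where the SFX-01 patient is better - pairs where worse) / all pairs. This is the quantity behind a rank test.

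| SFX-01 arm | All ranked | Non-completers dropped |
|---|---|---|
| 4 non-completers become poor-completed: 19/10/10/2/4 | (762 - 714)/2025 = +0.024 | (520 - 620)/1677 = -0.060 |
| 4 non-completers become good: 23/10/6/2/4 | (826 - 598)/2025 = +0.113 | (584 - 504)/1677 = +0.048 |
| 2 deaths become non-completers: 19/10/6/8/2 | (746 - 726)/2025 = +0.010 | (504 - 434)/1443 = +0.049 |

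Denominators are 45 × 45 = 2025, 39 × 43 = 1677 and 39 × 37 = 1443. The effect is reversed, more than halved and inflated in turn.

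Harm can also be hidden. With a control arm of 18/9/5/9/4 and an SFX-01 arm of 18/9/1/13/4, the figures are (713 - 769)/2025 = -0.028 with all ranked and (409 - 317)/1152 = +0.080 with non-completers dropped.

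**5. Against the 15% trigger.** 15% of 45 is 6.75, so 6 per arm (13.3%) requires no diagnostic. The first two rows of the table stay below the trigger. The third has 8/45 = 17.8% missing in the SFX-01 arm and would trigger section 6.7, as would the harm example (9/45 = 20% in controls). For these endpoints the trigger still yields only counts and a WFNS summary.

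**The case against.** **The premise is assumed.** The SAP gives no completion rates and does not say who fills in the forms. Proxy or assisted completion may be set out in the protocol, which is not at hand. This stands. If few living patients lack a form because of disability, the distortion is small.

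**Exclusion does not bias every analysis.** In a simulation with 45 per arm, an assumed SAHOT distribution, a uniform proportional-odds effect and 300 runs per odds ratio, dropping the worst living category gave median odds ratios of 2.00 and 3.00 at true values of 2 and 3. With everyone scored they were 2.10 and 3.11. Power fell from 50% to 43% and from 83% to 76%, with a standard error of 2 to 3 points on each figure. So a reader who infers that the rule always shrinks or reverses the effect goes too far. Distortion arises when treatment moves patients across the completion boundary or between death and non-completion, and it can favour either arm.

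**Death is not the worst score on every instrument.** A reader might infer that it is. For the SF-36 the weights in Table 6 contradict this (steps 1 and 2).

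**Section 6.7 is not silent below 15%.** It permits the diagnostics when results are marginal and leaves room for further analyses. That is correct, but the work is discretionary and no method is named.

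**The endpoints are lower-tier.** The SAP title calls efficacy exploratory. The primary endpoint is Doppler velocity, and the key secondaries are mRS and GOSE at 90 days, which grade severe living disability. This limits the weight of the point. The four questionnaires are nonetheless formally tested under section 6.5.

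**Conclusion.** The asymmetry is in the text for the SF-36, CLCE-24 and BICRO-39, and by evident intent for the SAHOT: deaths are scored, and living patients with unusable forms are excluded whatever the reason. No re-analysis is fixed for any of the four. If non-completion is partly due to severe disability, the treatment effect on these secondary endpoints can be shrunk, reversed or inflated. On the assumed counts, net win probability moves by 0.04 to 0.08 in the table and by 0.11 in the harm example.

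The sizes rest on assumed counts and on shifts chosen to show the mechanism. The documents do not show that severely disabled patients are in fact being lost, nor in which direction any bias would run. The primary endpoint and the key secondary endpoints are unaffected. The gap should be closed before unblinding.

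**What to change.** Add to Table 11 and section 6.7 one sensitivity analysis for these four endpoints that always runs, with no 15% trigger. A living patient without an evaluable form whose same-visit mRS is 5, or GOSE is 2 or 3, is placed at or below the worst living completers and above death:

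- **SAHOT:** category 8, the worst living category (tied with any completer there); death stays at 9.
- **BICRO-39 and SF-36:** a rank between the worst living completer and death. Set the SF-36 death rank directly as the lowest, because all-zero items give 20.1 and 17.3 and living patients can score lower.
- **CLCE-24:** an added level between the worst living score and death. For example, completers keep 0 to 3, these patients take 4 and deaths take 5. Placing them at 3 would give a score no living patient can reach on the emotional part and would tie them with death.

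Patients with neither an mRS nor a GOSE at that visit stay missing. Report by arm how many patients were ranked this way. In the same edit, correct the SAHOT completion rule under Table 9 so that it removes forms with fewer than half the items completed.

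Cost: SAP wording and one further run of existing models. mRS and GOSE are already scheduled at Days 28, 90 and 180, which covers every visit at which these questionnaires are collected. The small downside is that a clinician-rated scale sets the rank of a few questionnaire scores.

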**Table 5. SF36 subscale items**

| Subscale                                        | Number of Items | Item Numbers included  |
|-------------------------------------------------|-----------------|------------------------|
| Physical functioning (PF)                       | 10              | 3 4 5 6 7 8 9 10 11 12 |
| Role limitations due to physical health (RP)    | 4               | 13 14 15 16            |
| Role limitations due to emotional problems (RE) | 3               | 17 18 19               |
| Energy/fatigue (VT)                             | 4               | 23 27 29 31            |
| Emotional well-being (EW)                       | 5               | 24 25 26 28 30         |
| Social functioning (SF)                         | 2               | 20 32                  |
| Pain (BP)                                       | 2               | 21 22                  |
| General health (GH)                             | 5               | 1 33 34 35 36          |

**Table 6. SF-36 Reference Values and Physical and Mental Health Coefficients**

| Subscale | Mean  | SD    | PH Coefficient | MH Coefficient |
|----------|-------|-------|----------------|----------------|
| PF       | 84.52 | 22.89 | 0.42402        | -0.22999       |
| RP       | 81.20 | 33.80 | 0.35119        | -0.12329       |
| RE       | 81.29 | 33.03 | -0.19206       | 0.43407        |
| VT       | 61.05 | 20.87 | 0.02877        | 0.23534        |
| EW       | 74.84 | 18.01 | -0.22069       | 0.48581        |
| SF       | 83.60 | 22.38 | -0.00753       | 0.26876        |
| BP       | 75.49 | 23.56 | 0.31754        | -0.09731       |
| GH       | 72.21 | 20.17 | 0.24954        | -0.01571       |

PH = Physical Health, MH=Mental Health

## 5.8 CLCE-24

The Checklist for Cognitive and Emotional Consequences (CLCE-24) is recorded at 90 and 180 days. The CLCE-24 instrument consists of 24 questions with possible responses of 'No', 'Yes, but not severe', 'Yes, severely hindering daily life' and 'I am not sure'. The problems are split into cognitive problems, corresponding to the first 13 questions, and emotional problems, corresponding to the next 9 questions. The final 2 questions solicit information on

## EVG001SAH Statistical Analysis Plan

other specified problems; these will not be used in the analysis. Data will be analysed separately for emotional and cognitive problems. The number of questions, within each subscale, that has a response of either ‘Yes, severely hindering daily life’ or ‘Yes, but not severe’ will be calculated and this number will be recoded to a CLCE score as described in Table 7. The CLCE-24 score will be subject to statistical analysis.

If a patient dies before a given timepoint they will be assigned a score of 3. If less than 50% of the CLCE-24 questions are completed at a given timepoint the data will not be included in the analysis for that patient at that timepoint. Otherwise, the percentage of responses will be calculated using 24 as the denominator. In determining evaluability, a response of ‘I am not sure’ will be considered a completed response.

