## 6.5 Analysis of Secondary Efficacy Endpoints

The mRS, GOSE, SAHOT and CLCE will be analysed using a proportional odds logistic regression model to each timepoint separately including the following covariates: treatment, age (fitted as continuous variable), WFNS score (fitted as a class variable), hypertension (yes vs no), surgical procedure (clipping vs coiling vs none) and log-CRP. The treatment effect will be described using an odds ratio together with its likelihood ratio based 95% confidence interval. The statistical significance of the treatment effect will be taken from the chi-square test for the difference in deviance when removing treatment from the model. GOSE scores will be reversed prior to analysis so the odds of a better response is being modelled. PROC LOGISTIC can be used to analyse the data. If the model does not converge, any covariates that are not statistically significant will be removed in order from least significant until the model converges. If the model still does not converge, the outcome level with the fewest observations will be combined with the next most severe outcome and this process repeated until convergence is achieved.

BICRO and SF-36 will be analysed using Van-Elteren's test with 4 strata defined by age (above and below the median) and WFNS score (1-3 v 4-5). The treatment effect will be described using an un-stratified Hodges-Lehmann (HL) estimate of median difference together with its 95% confidence interval. The test can be implemented in SAS as follows:

```

proc npar1way data=data1 HL;
  strata strata/wilcoxon;
  class trt;
  var resp;
run;

```

The proportion of patients with delayed cerebral ischaemia, new cerebral infarct and receiving triple H therapy will be analysed using logistic regression with the same set of covariates used for mRS. The statistical significance of the treatment effect will be taken from the chi-square test for the difference in deviance when removing treatment from the model. The treatment

effect will be described in terms of an odds ratio together with its likelihood ratio based 95% confidence interval.

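### CLCE-24 is tested on four wide bands rather than the problem count the planned proportional odds model could use, at a likely cost of a few points of power

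*SAP*

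**What the plan says.** Section 5.8 defines two subscales: "The problems are split into cognitive problems, corresponding to the first 13 questions", and "emotional problems, corresponding to the next 9 questions". It adds: "Data will be analysed separately for emotional and cognitive problems". Within each subscale it counts the items answered as a problem, severe or not. Then "this number will be recoded to a CLCE score as described in Table 7. The CLCE-24 score will be subject to statistical analysis". Table 7 gives 0 for no problems, 1 for under 25%, 2 for 25% to under 50%, and 3 for 50% or more. For evaluable questionnaires, "the percentage of responses will be calculated using 24 as the denominator". On death: "If a patient dies before a given timepoint they will be assigned a score of 3".

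Section 6.5 sets the test: "The mRS, GOSE, SAHOT and CLCE will be analysed using a proportional odds logistic regression model to each timepoint separately". Table 11 lists the CLCE-24 analysis at Days 90 and 180. Section 6.3 names mRS and GOSE at 90 days as the key secondary endpoints; CLCE-24 is not among them.

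**The concern.** The count is already an ordered outcome, and the planned model takes an ordered outcome with any number of levels. Cutting it to four codes first discards information. The SAP gives no reason or source for the cut points, whereas Section 5.10 cites a published categorisation for SAHOT. At stake is sensitivity for two outcomes at two timepoints.

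There is also an inconsistency over death. Sections 5.2, 5.3 and 5.10 give death its own level for mRS, GOSE and SAHOT, which share the model. On the cognitive CLCE-24 score, death shares a level with the worst-affected survivors.

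**Working it through.** **1. Bands as written.** With 24 as denominator, 25% is 6 problems and 50% is 12.

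- Cognitive: 5/24 = 20.8%, 6/24 = 25%, 11/24 = 45.8%, 12/24 = 50%. Levels: 0 | 1–5 | 6–11 | 12–13 plus death.
- Emotional: the maximum is 9/24 = 37.5%, so no survivor can reach score 3. Levels: 0 | 1–5 | 6–9 | death only.

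**2. Bands if each subscale were its own denominator.**

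- Cognitive: 3/13 = 23.1%, 4/13 = 30.8%, 6/13 = 46.2%, 7/13 = 53.8%. Levels: 0 | 1–3 | 4–6 | 7–13 plus death.
- Emotional: 2/9 = 22.2%, 3/9 = 33.3%, 4/9 = 44.4%, 5/9 = 55.6%. Levels: 0 | 1–2 | 3–4 | 5–9 plus death.

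**3. The plan's own power figure.** Section 3.1 covers only the TCD endpoint. With 45 per arm, one-sided 5% and a difference of 0.53 SD, power is Φ(0.53 × √(45/2) − 1.645) = Φ(0.869) = 80.8%. With two-sided 5% and 0.59 SD it is Φ(0.59 × √(45/2) − 1.960) = Φ(0.839) = 79.9%. So 45 per arm fits the plan, provided the ratio is read as difference over SD; the SAP words it the other way round, which is a separate matter. No power is stated for CLCE-24.

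**4. Simulation of the banding loss.**

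From the SAP: 90 evaluable patients, two-sided 5%, 13 and 9 items, Table 7, the death rule. Assumed: 1:1 allocation; beta-binomial counts with mean proportion μ and intra-class correlation ρ, so α = μ(1−ρ)/ρ and β = (1−μ)(1−ρ)/ρ; the death rate; and an odds ratio chosen for about 80% power on the full count with death ranked worst. The effect is logit P(Y ≤ j | SFX-01) = logit P(Y ≤ j | placebo) + log OR. The test is the tie-corrected Wilcoxon, which is the score test of the unadjusted proportional odds model. Loss = power on the full count minus power on the bands.

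Narrow grid (μ 20–50%, ρ 0.15–0.30, deaths 5–15%; OR about 2.8–3.0), bands as written:

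| Subscale | Median loss (points) | Range |
|---|---|---|
| Cognitive | 6.2 | 2 to 13 |
| Emotional | 7.5 | 2 to 21 |

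A separate run gave medians of 5.6 and 7.3. With subscale denominators the narrow-grid median is about 2 to 3 points (range 0.5 to 5.7).

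Wider grid (μ 15–65%, ρ 0.10–0.35, deaths 5–20%), medians with ranges:

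| Denominator, effect | Cognitive | Emotional |
|---|---|---|
| 24, proportional odds | 6.5 (0.4 to 17.6) | 7.1 (0.5 to 26.6) |
| 24, survivors only | 8.0 (−4.7 to 28.5) | 11.8 (−0.2 to 41.3) |
| Subscale, proportional odds | 3.9 (0.4 to 20.1) | 2.8 (−0.2 to 18.5) |
| Subscale, survivors only | −2.0 (−12.9 to 8.0) | −3.4 (−14.2 to 6.2) |

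**5. Where the loss comes from.** Keeping the bands on 24 but giving death its own code leaves the proportional odds median at 6.5 for cognitive. It gives 6.9 against 7.1 for emotional, where death is already alone, so that difference is simulation noise. The wide middle bands cause the loss. In the subscale, survivors-only case, a separate death code turns −2.0 and −3.4 into losses of 4.8 and 3.1. The reversal therefore comes from pooling deaths with many survivors, not from a merit of the cut points.

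**The case against.** The strongest reply has four parts.

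- **The size rests on assumptions.** The SAP gives no count distribution, death rate or effect for CLCE-24, and the main scenarios generate the effect under the model that favours the count. This stands: the figure is a range under stated inputs, not a property of the plan.
- **The size depends on the denominator.** Most of the 6 to 7 points arises because 24 is applied to subscales of 13 and 9 items. With subscale denominators the loss is small and its sign depends on the effect. This also stands, but 24 is what the SAP specifies.
- **More levels have a price.** The count gives up to 15 cognitive levels (14 counts plus death) and 11 emotional levels in about 90 patients. On non-convergence, Section 6.5 removes non-significant covariates first and merges levels only afterwards. This is a real but small downside.
- **The endpoint is minor.** Efficacy is exploratory by the study title and CLCE-24 is not a key secondary. Prespecified bands without a cited source are not in themselves an error. Both points limit the consequence.

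A reader might also infer that death ties with survivors on both subscales. As written it does not, because the emotional maximum is 37.5%. On the cognitive subscale the tie needs 12 or 13 of 13 problems, about 0.2% to 12% of survivors under the narrow-grid assumptions. Nor do most survivors always tie: the cognitive 1–5 band holds 36% to 65% of them. And separate death levels are not universal in the SAP: SF-36 and BICRO-39 give death the worst questionnaire score without one.

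**Conclusion.** The point holds in limited form. Section 5.8 bands an ordinal count that the planned model could use whole. As written, with a proportional odds effect and the narrow-grid inputs, this costs a median of about 6 to 7 points of power (range about 2 to 20). If the effect were in survivors only, the medians would be about 8 to 12. With subscale denominators the loss is about 2 to 4 points under proportional odds, and it can vanish or reverse slightly with a survivors-only effect. All these figures omit the model covariates.

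The documents do not support reading the death code as a cause of lost power under the written rule. The cognitive death tie is a matter of interpretation and of consistency with mRS, GOSE and SAHOT. Giving death a score of 4 while keeping the bands would settle that tie but recover essentially no power. The consequence is confined to two non-key secondary outcomes.

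**What to change.** In Sections 5.8, 6.2 (Table 11) and 6.5, analyse the subscale problem count in the planned proportional odds model, with death as one further level worse than the maximum (15 levels cognitive, 11 emotional). Keep the Table 7 bands for the descriptive table only. This also takes the ill-fitting denominator of 24 out of the test. The 50% completion rule can stay; the SAP should then say explicitly that unanswered items add nothing to the count, as is already the effect of the fixed denominator.

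The cost is SAP wording and a short change to the derivation code, with no new data. The downside is more sparse levels, which may trigger the Section 6.5 non-convergence rule and so drop covariates before any levels are merged.
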